#### Safety analysis

AEs will be recorded at each visit through spontaneous reporting and systematic questioning. The incidence, severity, and causality (relatedness to intervention) of AEs will be summarized using descriptive statistics and compared between groups using Fisher’s exact test or chi-square test.

#### Cost-effectiveness analysis

Cost-effectiveness evaluation will be primarily based on the full analysis set (FAS), with a per-protocol (PP) analysis conducted to assess sensitivity to missing data. Estimation of utility and cost will follow the same approach used in the clinical effectiveness evaluation, with missing data handled using appropriate imputation methods based on the identified mechanisms.

The decision tree model will be employed as the primary modeling framework for the cost-effectiveness evaluation. As economic evaluation indices, the Incremental Cost-Utility Ratio (ICUR), based on the EQ-5D-5 L results and cost data, and the Incremental Cost-Effectiveness Ratio (ICER), based on individual clinical outcome indicators and cost data, are calculated using the following formulas:$$\:\mathrm{I}\mathrm{C}\mathrm{U}\mathrm{R}=\frac{\mathrm{T}\mathrm{o}\mathrm{t}\mathrm{a}\mathrm{l}\:{\mathrm{C}\mathrm{o}\mathrm{s}\mathrm{t}}_{\mathrm{C}\mathrm{P}\:\mathrm{g}\mathrm{r}\mathrm{o}\mathrm{u}\mathrm{p}}-\:\mathrm{T}\mathrm{o}\mathrm{t}\mathrm{a}\mathrm{l}\:{\mathrm{C}\mathrm{o}\mathrm{s}\mathrm{t}}_{\mathrm{U}\mathrm{s}\mathrm{u}\mathrm{a}\mathrm{l}\:\mathrm{C}\mathrm{a}\mathrm{r}\mathrm{e}\:\mathrm{G}\mathrm{r}\mathrm{o}\mathrm{u}\mathrm{p}}}{{\mathrm{Q}\mathrm{A}\mathrm{L}\mathrm{Y}}_{\mathrm{C}\mathrm{P}\:\mathrm{g}\mathrm{r}\mathrm{o}\mathrm{u}\mathrm{p}}-\:{\mathrm{Q}\mathrm{A}\mathrm{L}\mathrm{Y}}_{\mathrm{U}\mathrm{s}\mathrm{u}\mathrm{a}\mathrm{l}\:\mathrm{C}\mathrm{a}\mathrm{r}\mathrm{e}\:\mathrm{G}\mathrm{r}\mathrm{o}\mathrm{u}\mathrm{p}}}$$$$\:\mathrm{I}\mathrm{C}\mathrm{E}\mathrm{R}\:=\frac{\mathrm{T}\mathrm{o}\mathrm{t}\mathrm{a}\mathrm{l}\:{\mathrm{C}\mathrm{o}\mathrm{s}\mathrm{t}}_{\mathrm{C}\mathrm{P}\:\mathrm{g}\mathrm{r}\mathrm{o}\mathrm{u}\mathrm{p}}-\mathrm{T}\mathrm{o}\mathrm{t}\mathrm{a}\mathrm{l}\:{\mathrm{C}\mathrm{o}\mathrm{s}\mathrm{t}}_{\mathrm{U}\mathrm{s}\mathrm{u}\mathrm{a}\mathrm{l}\:\mathrm{C}\mathrm{a}\mathrm{r}\mathrm{e}\:\mathrm{G}\mathrm{r}\mathrm{o}\mathrm{u}\mathrm{p}}}{{\mathrm{E}\mathrm{f}\mathrm{f}\mathrm{e}\mathrm{c}\mathrm{t}}_{\mathrm{C}\mathrm{P}\:\mathrm{g}\mathrm{r}\mathrm{o}\mathrm{u}\mathrm{p}}-{\mathrm{E}\mathrm{f}\mathrm{f}\mathrm{e}\mathrm{c}\mathrm{t}}_{\mathrm{U}\mathrm{s}\mathrm{u}\mathrm{a}\mathrm{l}\:\mathrm{C}\mathrm{a}\mathrm{r}\mathrm{e}\:\mathrm{G}\mathrm{r}\mathrm{o}\mathrm{u}\mathrm{p}}}$$

One-way and probabilistic sensitivity analyses will be conducted to assess the robustness of the results. In the sensitivity analysis, deterministic sensitivity analysis will be performed for all relevant parameters and visualized through a tornado diagram, followed by probabilistic sensitivity analysis using parameter distributions and representative values.

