**Methods:**

This will be a single-center, randomized, assessor-blinded, parallel-group clinical trial. A total of 30 eligible participants aged 19 to 70 years with chronic TMD (VAS ≥ 40 mm for ≥ 3 months) will be randomized 1:1 to either the experimental group (TBT) or the control group (Transcutaneous Electrical Nerve Stimulation, TENS). Both interventions will be administered twice a week for 6 weeks (12 sessions). The primary outcome is the mean change in temporomandibular joint pain measured by the Visual Analog Scale (VAS, 100 mm) at 6 weeks compared to baseline. Secondary outcomes include worst TMD pain VAS, jaw range of motion (pain-free opening, maximum unassisted opening), Jaw Functional Limitation Scale (JFLS-8), DC/TMD Graded Chronic Pain Scale (GCPS 2.0), Treatment Expectancy Scale, Patient Global Impression of Change (PGIC), quality-adjusted life years (QALYs), EQ-5D, EQ-VAS, medical costs, lost productivity costs, and incremental cost-effectiveness ratio (ICER). Data will be collected at baseline, 6 weeks, and 10 weeks (for follow-up). Statistical analysis will compare outcomes between groups using appropriate methods, primarily intention-to-treat analysis.

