## Methods/design

### Study design

This study will be a single-center, randomized, assessor-blinded, active-controlled, parallel-group clinical trial designed to evaluate the efficacy, safety, and cost-effectiveness of TBT for TMD. A total of 30 participants will be recruited and randomly assigned in a 1:1 ratio to the TBT experimental group and TENS control group. The study consists of a screening visit, 12 treatment visits over 6 weeks (twice weekly), and a follow-up visit at week 10. The detailed study design is summarized in Fig. 1; Table 1. This protocol adheres to the Standard Protocol Items: Recommendations for Interventional Trials (SPIRIT) 2013 guidelines and checklist (Supplementary material 1) [24]. The flowchart of this study is shown in Fig. 1. The SPIRIT schedule of enrollment, interventions, and assessments is shown in Fig. 2.

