### Cost-effectiveness evaluation

A cost-effectiveness evaluation will be conducted based on the cost and outcome data collected during this study to compare the cost-effectiveness between the intervention group and the control group. The primary analysis period is set at 10 weeks (corresponding to the study’s follow-up duration). If projection beyond these 10 weeks is required, long-term modeling such as a Markov model will be used. When the total analysis period (time horizon) exceeds 12 months, all costs will be standardized to 2024 Korean Won (KRW), and a 4.5% annual discount rate will be applied, based on the HIRA economic evaluation guidelines.

Effectiveness will be estimated using Quality-Adjusted Life Years (QALYs) and individual clinical outcome indicators measured according to the clinical trial schedule after randomization. QALYs will be measured using the validated Korean version of EQ-5D-5 L and calculated using the Korean-specific tariff developed by Kim et al. (2016) [27]. Individual effectiveness indicators will be derived from the primary and secondary clinical outcome measures as defined in the trial protocol.

Cost estimation will be performed using a micro-costing approach that multiplies the unit cost by usage volume for each cost item. Institutional data on resources and time required for TBT and TENS procedures will be collected internally. Participant-level cost data will be collected through surveys administered at Week 0, Week 6, and Week 10, capturing costs incurred over the preceding six weeks. Productivity losses will be assessed using the WPAI: GH 2.0 instrument, which evaluates productivity loss over the previous seven days. These results will be extrapolated using interpolation to estimate productivity losses over six weeks.

The analysis will be conducted from both the healthcare system perspective (including direct medical costs) and the societal perspective (including direct medical costs, non-medical costs, and productivity losses). Because the primary analysis period is less than one year, discounting will not be applied.

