### Assignment of interventions

#### Allocation

The randomization process will be managed by a statistician who is not involved in the conduct or assessment of the clinical trial. The randomization officer will generate the randomization list using a specifically planned and reproducible method, employing Python 3.12.4 (Python Software Foundation, Wilmington, DE, USA) to ensure equal probability of assignment for each participant. Block randomization will be used to maintain balance between groups, with participants allocated to the intervention (TBT) and control (TENS) groups in a 1:1 ratio.

The randomization list will be sealed and stored in a manner that allows confirmation of whether the seal has been broken, and will be managed separately by the principal investigator. For allocation, the study coordinator will open the randomization envelopes sequentially in front of the participant at the time of assignment. Each opened envelope will have the date of opening and the study coordinator’s signature recorded and will be stored separately for documentation.

Participants who provide written informed consent and undergo screening will be assigned a screening number in the format DJ-S-001 (where DJ refers to Daejeon University Daejeon Korean Medicine Hospital, S indicates Screening, and 001 is the serial number). Only those who meet the inclusion and exclusion criteria after the eligibility assessment will be assigned a subject identification code in the format DJ-E-001 (where E indicates Enrollment).

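### The ICUR and ICER formulas name two groups that this trial does not have, and the text does not secure adjustment of incremental QALYs for baseline utility

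*Protocol article*

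**What the plan says.** On the arms, the article is consistent everywhere except in the formulas. Under Study design, participants are "randomly assigned in a 1:1 ratio to the TBT experimental group and TENS control group". Allocation repeats this, "with participants allocated to the intervention (TBT) and control (TENS) groups in a 1:1 ratio". Cost-effectiveness evaluation sets out "to compare the cost-effectiveness between the intervention group and the control group".

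Cost-effectiveness analysis then defines the two ratios, beginning "As economic evaluation indices, the Incremental Cost-Utility Ratio (ICUR), based on the" EQ-5D-5L and costs. The ICER is "based on individual clinical outcome indicators and cost data, are calculated using the following formulas". Each printed formula has four terms (two costs, and two QALYs or two effects). Every term is labelled either CP group or Usual Care Group. CP is not explained in the text or in the Abbreviations list.

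On estimation, the same section says: "Estimation of utility and cost will follow the same approach used in the clinical effectiveness evaluation". Cost-effectiveness evaluation adds: "Effectiveness will be estimated using Quality-Adjusted Life Years (QALYs) and individual clinical outcome indicators". The Abstract gives the measurement times: "Data will be collected at baseline, 6 weeks, and 10 weeks (for follow-up").

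**The concern.** There are two separate matters.

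First, these are the only equations that define the economic endpoints, and they name the wrong groups. Cost-effectiveness is one of the three stated aims of the trial, and the Discussion expects the results to reach guideline writers and policymakers. A ratio labelled as being against usual care would describe a comparison that was not randomized.

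Second, a QALY built from utilities at weeks 0, 6 and 10 contains the baseline utility itself. In a small trial the arms will differ at baseline by chance, and an unadjusted QALY difference carries that chance difference with it. Over 10 weeks any real QALY gain is small, so the carried amount may be of similar size and could change the sign of the denominator of the ICUR. The primary pain outcome has an explicit safeguard against this (ANCOVA on baseline VAS). The economic outcome has only a cross-reference.

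**Working it through.** **What the cross-reference resolves to.** The clinical evaluation contains more than one approach:

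- Primary outcome analysis specifies ANCOVA, and the only covariate it names is baseline pain VAS.
- Secondary outcome analysis specifies linear mixed models for continuous outcomes measured repeatedly. Its list of outcomes does not include EQ-5D, QALYs or costs, although the Abstract lists them as secondary outcomes.

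The cross-reference does not say which approach applies. Taken literally, the first would adjust QALYs for pain, which is not the same as adjusting for baseline utility. An analyst could follow the text and compute unadjusted increments, or could adjust.

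**Number per arm.** From Sample size calculation and statistical hypotheses: 2 × (1.96 + 1.28)² × 1.5² / 2² = 11.81, rounded up to 12. Then 12 / (1 − 0.20) = 15 per arm, 30 in total. The plan's figure reproduces and is not affected by this point.

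**Inputs for the illustration.** From the document: 15 per arm, visits at weeks 0, 6 and 10. Assumed, because the document gives none of them: utility SD 0.05 to 0.20, the same at every visit; one common correlation ρ between visits of 0.3 to 0.7; a true utility gain of 0.05 reached by week 6 and held to week 10; QALYs by the trapezoidal rule.

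**Weights.** The trapezoids over weeks 0–6 and 6–10 give weights of 3/52 on baseline, (3 + 2)/52 = 5/52 on week 6 and 2/52 on week 10.

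**Value of the assumed gain.** (0.05 / 2) × 6/52 + 0.05 × 4/52 = 0.35/52 = 0.0067 QALY.

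**Chance baseline difference.** SE = SD × √(2/15). This is 0.018 at SD 0.05, 0.037 at SD 0.10 and 0.073 at SD 0.20.

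**Shift in the unadjusted QALY difference for a one-SE baseline difference.** Shift = SE × (3 + 7ρ)/52:

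| Utility SD | ρ = 0.3 | ρ = 0.5 | ρ = 0.7 |
|---|---|---|---|
| 0.05 | 0.0018 | 0.0023 | 0.0028 |
| 0.10 | 0.0036 | 0.0046 | 0.0055 |
| 0.15 | 0.0054 | 0.0068 | 0.0083 |
| 0.20 | 0.0072 | 0.0091 | 0.0111 |

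At SD 0.10 and ρ = 0.5, a one-SE imbalance equals 0.0046 / 0.0067, or about two thirds, of the assumed gain. At SD 0.15 and ρ = 0.5 it slightly exceeds the gain.

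**Precision with and without adjustment (SD 0.10, ρ = 0.5).**

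- Variance of one participant's QALY: 0.10² × [(9 + 25 + 4) + 2 × 0.5 × (15 + 6 + 10)] / 52² = 0.01 × 69/2704 = 0.000255.
- Part explained by baseline utility: 0.01 × (6.5/52)² = 0.000156.
- SE of the difference, unadjusted: √(0.000255 × 2/15) = 0.0058.
- SE of the difference, adjusted: √((0.000255 − 0.000156) × 2/15) = 0.0036.

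**The case against.** The best counter-argument is the cross-reference itself. A ratio formula defines an index and does not say how the increments are estimated. The article says that utility and cost are estimated as the clinical outcomes are, and the primary clinical analysis adjusts for baseline. This stands to the extent that a reader might infer a commitment to raw mean differences, and the document does not support that inference. It leaves the estimator open, because the reference points to more than one method and to a covariate that is not utility.

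A second objection is that an explicit utility covariate is detail that an article leaves to the full protocol or analysis plan, neither of which is shown. That has weight against calling it an omission. It does not help the formulas, which the article prints in full with the wrong groups.

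Third, the label error may be called editorial. The intended comparator can be recovered from the rest of the article, which also plans to collect resource data for the TBT and TENS procedures. A reader might infer that inference against usual care is planned, but nothing outside the formulas says so. The labels are still wrong as printed.

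Fourth, the magnitudes rest on assumptions, and under randomization chance imbalance is sampling error, not bias. Both are true. Adjustment is also no cure. At the adjusted SE of 0.0036, a gain of 0.0067 has a 95% interval of 0.0067 ± 1.96 × 0.0036, about −0.0004 to 0.0138, so the sign stays uncertain. What remains is a worthwhile gain in precision from data already planned.

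**Conclusion.** The label error holds without qualification: both formulas contrast groups that do not exist in this trial. The adjustment point holds in limited form: the text does not secure adjustment for baseline utility, though it does not rule it out.

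The likely size of an unadjusted one-SE imbalance is about 0.002 to 0.011 QALY, against 0.0067 for a sustained gain of 0.05. This is conditional on the assumed SDs, correlations, effect and trapezoidal rule. The primary clinical analysis and the sample size are untouched. The change is worth making because cost-effectiveness is a stated aim and the ICUR denominator will be very small.

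**What to change.** In both formulas, replace CP group with TBT and Usual Care Group with TENS. In place of the cross-reference on utility and cost estimation, state that incremental QALYs come from a regression of each participant's QALY on arm and baseline EQ-5D utility, that incremental costs come from a regression on arm and week-0 cost, and that these adjusted increments enter the ratios.

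Two additions are optional: a bootstrap that resamples participants with cost and QALY kept paired, and a sentence saying that no comparison with usual care is made.

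The cost is a few lines of text and code. Baseline data collection and the week-0 cost survey are already planned, so no new data are needed.

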## Ethics and dissemination

The clinical trial will be performed under the Declaration of Helsinki, Korean GCP Guidelines, related laws, and protocols. This study was approved by the Institutional Review Board (IRB) of Daejeon University Daejeon Korean Medicine Hospital (approval number: DJDSKH-24-BM-13-1) on 4 November 2024. This study was registered in April 2025 at the National Clinical Trial Registry Clinical Research Information Service (https://cris.nih.go.kr) with the identifier number KCT0010382.

## Discussion

This study protocol outlines a single-center, randomized, assessor-blinded, parallel-group clinical trial designed to evaluate the effectiveness, safety, and cost-effectiveness of TBT compared to TENS for patients with TMD. Given the increasing prevalence and economic burden of TMD, coupled with the recognized gaps in current clinical practice guidelines regarding intraoral balancing appliances, this trial is poised to contribute significantly to the evidence base for TMD management.

The rising trend in TMD patient numbers and healthcare costs in South Korea underscores the urgent need for effective and economically viable treatment options. While various conventional treatments exist, the limitations of current pharmacotherapies (e.g., side effects of NSAIDs, muscle relaxants, antidepressants) and the uncertain evidence for widely used interventions like occlusal splints highlight the necessity for exploring alternative, evidence-based therapies. Our study addresses a critical unmet need by focusing on TBT, a novel Korean medicine approach utilizing intraoral balancing appliances, which has yet to be assessed through a randomized controlled trial.

A key strength of this protocol lies in its design, including randomization and assessor blinding, which aims to minimize bias and enhance the internal validity of the findings. The comprehensive set of outcome measures, encompassing pain intensity, jaw function, chronic pain grading, patient-reported outcomes, and a thorough economic evaluation, will provide a holistic understanding of TBT’s impact. Furthermore, the inclusion of an economic feasibility analysis is particularly relevant in the context of rising healthcare expenditures, offering insights into the cost-effectiveness of TBT in a real-world clinical setting. The use of a standard TENS therapy as a control group, a commonly utilized and relatively well-established physical therapy modality for TMD, allows for a direct comparison with a widely accepted intervention.

However, several practical and operational difficulties must be examined during this trial. As a single-center study, the generalizability of our findings to a larger population or different clinical settings might be limited. We intend to address this by clearly defining inclusion and exclusion criteria to ensure a homogeneous patient population. To further address the generalizability, our research team is also planning a multi-center registry study, a prospective observational study, involving various Korean medical clinics and hospitals that currently implement TBT. This will allow for the collection of real-world data from a more diverse patient population and across different clinical environments, thereby enhancing the external validity of TBT’s effects.

Participant and practitioner blinding is not feasible given the nature of the interventions, which could introduce some performance or detection bias. To address this, we have implemented assessor blinding for all outcome measurements and standardized treatment protocols to ensure consistency in intervention delivery. However, it is important to acknowledge that the lack of participant and practitioner blinding might lead to differential treatment expectancy or performance bias between groups, potentially influencing subjective outcomes. While objective measures are less susceptible, the interpretation of patient-reported outcomes (e.g., VAS, PGIC, Treatment Expectancy Scale) should consider this limitation.

In conclusion, this protocol describes a meticulously designed randomized controlled trial that will provide crucial evidence on the efficacy, safety, and economic viability of TBT for TMD. The findings are expected to inform future clinical practice guidelines, particularly those related to Korean medicine interventions for TMD, and offer valuable insights for clinicians and policymakers seeking effective and sustainable treatment strategies.

### Trial status

Protocol version number: 1.3, date: 13 January 2025.

The date recruitment began: 11 February 2025.

The approximate date when recruitment will be completed: 30 June 2025.

## Data Availability

All data necessary to support the findings of this study are available within the manuscript and/or its supplementary information files. The full study protocol, as approved by the institutional review board, is provided as a supplementary file (S2 Appendix). The findings of this study will be disseminated through publication in a peer-reviewed scientific journal. An anonymized participant-level dataset and statistical code used for the analyses will be made available from the corresponding author upon reasonable request, provided that the request aligns with ethical guidelines and participant privacy protection. This data will be available after the publication of the main study results.

## Abbreviations

AEs: Adverse Events
ANCOVA: Analysis of Covariance
BTX: Botulinum toxin
C2: Axis (C2 cervical vertebra)
CBA: Customized Balancing Appliance
CBT: Cognitive Behavioral Therapy
CEAC: Cost-Effectiveness Acceptability Curve
CIs: Confidence Intervals
CRIS: Clinical Research Information Service
DC/TMD: Diagnostic Criteria for Temporomandibular Disorders
eCRF: electronic Case Report Form
EMR: Electronic Medical Records
EQ-5D: EuroQol Five Dimensions
EQ-VAS: EuroQol Visual Analogue Scale
FAS: Full Analysis Set
FCST: Functional Cerebrospinal Therapy
GCP: Good Clinical Practice
GCPS 2.0: Graded Chronic Pain Scale 2.0
HIRA: Health Insurance Review & Assessment Service
ICER: Incremental Cost-Effectiveness Ratio
ICF: Informed Consent Form
ICUR: Incremental Cost-Utility Ratio
IADR: International Association for Dental, Oral, and Craniofacial Research
INfORM: International Network for Orofacial Pain and Related Disorder Methodology
IRB: Institutional Review Board
ITT: Intention-To-Treat
JFLS-8: Jaw Functional Limitation Scale-8
KRW: Korean Won
LLLT: Low-Level Laser Therapy
MAR: Missing at Random
MFDS: Ministry of Food and Drug Safety
NSAIDs: Non-Steroidal Anti-Inflammatory Drugs
O-C2: Occiput-C2
PGIC: Patient Global Impression of Change
PP: Per-Protocol
QALYs: Quality-Adjusted Life Years
RCT: Randomized Controlled Trial
SAEs: Serious Adverse Events
SD: Standard Deviation
SOPs: Standard Operating Procedures
SPIRIT: Standard Protocol Items: Recommendations for Interventional Trials
TBT: Temporomandibular Joint Balancing Therapy
TENS: Transcutaneous Electrical Nerve Stimulation
TMJ: Temporomandibular Joint
TMD: Temporomandibular Joint Disorder
VAS: Visual Analog Scale
WPAI: GH 2.0:Work Productivity and Activity Impairment: General Health 2.0
